### 2.7. Intervention

Experimental group: Participants will perform the SSE intervention program twice a week for 9 weeks. The instructors will receive initial training on ASD (characteristics, strengths, motivation, and disruptive behaviour management techniques) and will be familiarised with the participants before starting the intervention. The training sessions will last approximately 30 min, and their basic structure is shown in Table 2. The first activity will be a general warm-up; then, the participants will learn and execute the selected patterns for that day, and they all should be repeated 5 times. The session will finish with a cool-down.

Participants will start with movement patterns such as walking, and little by little, they will make more complex patterns that will require multidirectional movements. Participants should not step on the squares’ dividing lines. The instructor will mark every attempt in an individual notebook where the patterns will be registered, providing information on whether they were performed correctly, with errors or with assistance, and qualitative observations can be added. An example can be found in Figure 1.

The SSE has some strengths when used with children and adolescents with ASD: (1) it is simple; the repetitive and easy-to-follow structure provides the anticipation, routine, and comprehension that some children with ASD diagnoses need, promoting errorless teaching that can help participants with self-regulation issues; (2) at the same time, it is flexible, as it offers the possibility to add additional elements, such as songs, colours, balloons, visual aids, and others, which could improve the adherence and pleasure during the training sessions. Table 3 displays the proposed progression of the SSE sessions.

Control group: Participants with ASD will continue with their usual treatments and will only be present for the assessment sessions. An additional control group of age-matched, typically developed children will be added because this intervention is rarely used in children in general.

Both groups will perform evaluations at the beginning of the program, the end of the program, and a follow-up after one month following the end of the training sessions, using the described tools: MACB-2 (balance sections and behavioural checklist), SP2 (child version), the FACES, EFECO-S and Ring and Interference tasks from the ENFEN.

### 2.8. Statistical Analysis

The Statistical Package for the Social Sciences (SPSS, Version 25, IBM SPSS, Armonk, NY, USA) software will be used to perform the analyses.

Data normality and homogeneity will be assessed with the Kolmogorov–Smirnov test and Levene’s test. Descriptive data will be expressed as means and standard deviation (SD) (for normally distributed variables) or medians and interquartile range (for non-normally distributed variables). Then, data will be analysed by intention-to-treat and protocol.

Intention-to-treat analysis. All randomised participants will be considered for the analysis in its group. Missing data will be imputed through multiple imputations. Repeated measures analyses of covariance adjusted by age and baseline outcomes will be used to analyse the intervention effects on the different dependent variables. The effect sizes (95% confidence interval) and differences will be calculated for every variable concerning the time and group × time interaction. The alpha level will be set at *p* < 0.05. The data imputation for sensitivity analyses will be carried out on individuals who present data at baseline and at the end of the trial to prevent estimation bias [66].

Analysis by protocol. The analyses previously described will be carried out, but only for participants who attend at least 80% of the program sessions.

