### 2.4. Eligibility Criteria

Participants will meet the following criteria: (a) age between 6 and 12 years; (b) a clinical ASD diagnosis under The Diagnostic and Statistical Manual of Mental Disorders, Fifth Edition [5]; (c) ability to understand and follow simple commands; (d) no inconvenience that prevents physical activity; (e) children and adolescents’ voluntariness to take part in the study; and (f) provide signed informed consent form by the legal guardians. The experimental group individuals should complete at least 80% of the sessions and all the evaluations to be considered in the analysis.

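### The sensitivity imputation leaves out children with no end-of-trial value, so it cannot test the main imputation's assumption about them and does not prevent bias as claimed

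*Protocol article*

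**What the plan says.** All the relevant statements but one stand in the intention-to-treat paragraph of Section 2.8 of the protocol article.

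- Population: "All randomised participants will be considered for the analysis in its group".
- Missing data: "Missing data will be imputed through multiple imputations".
- Model: "Repeated measures analyses of covariance adjusted by age and baseline outcomes will be used to analyse the intervention effects".
- Sensitivity analysis: "The data imputation for sensitivity analyses will be carried out on individuals who present data at baseline and at the end of the trial". The sentence closes with its reason, "at the end of the trial to prevent estimation bias", and a citation.

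Section 2.7 sets three assessments: "evaluations at the beginning of the program, the end of the program, and a follow-up after one month" after the training ends. The article does not say whether the end of the trial is the second or the third of these.

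The other supporting analysis in Section 2.8, by protocol, is run "only for participants who attend at least 80% of the program sessions". It too restricts the population and makes no different assumption about missing outcomes.

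**The concern.** Multiple imputation fills in missing outcomes under an assumption that the observed data cannot verify. A sensitivity analysis for missing data exists to vary that assumption for the children it concerns. The stated rule instead requires an observed end-of-trial value, so the children whose final outcome is unknown are not in it. What is left to impute is one other visit, or single items and scales.

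What is at stake is false reassurance. Suppose dropout is related to how a child does on the programme, and the imputation draws only on baseline, age and arm for a child with no later data. Imputation under a missing-at-random assumption and a baseline-adjusted completers analysis will then give much the same estimate. Their agreement would look like robustness but would say nothing about the children who left.

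**Working it through.** The challenged sentence contains no figure, and the article gives no dropout rate. The first step is therefore a reading of the text. The later steps are illustrations on assumed values.

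**1. Who is left out.**

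| Child | End of trial = end of programme | End of trial = one-month follow-up |
|---|---|---|
| Lost during the programme, no later assessment | out | out |
| Assessed at end of programme, lost before follow-up | in | out |
| Stops sessions but attends all assessments | in | in |

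On either reading, children lost during the programme without a final assessment are out. The middle row depends on the undefined term.

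**2. Arm size.** Section 2.3 gives 26 per arm, 52 in total. This reproduces if its effect size of 0.40 is read as Cohen's f: two groups, two-sided 0.05 and 80% power need 51.05, hence 52. Only the 26 is used below.

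**3. Size of bias in the completers estimate, one arm affected.** Assumptions: a fraction p of the exercise arm is lost and nobody in the control arm; those lost are the lowest on a latent score; that score correlates 0.5 with the baseline-adjusted outcome; baseline and outcome correlate 0.6; there is no true effect.

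- Residual SD after baseline adjustment: √(1 − 0.6²) = 0.8.
- Mean latent score of those who stay: φ(z_p)/(1 − p).
- Bias = φ(z_p)/(1 − p) × 0.5 × 0.8.
- p = 20%: 0.280/0.80 × 0.5 × 0.8 = **0.14 SD**, with about 5 children missing (0.20 × 26 = 5.2).
- p = 30%: 0.348/0.70 × 0.5 × 0.8 = **0.20 SD**, with about 8 children missing (0.30 × 26 = 7.8).
- Same mechanism equally in both arms, no effect: the shifts cancel (0.14 − 0.14 = 0).

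**4. Is the restriction ever protective?** A large simulation used a true effect of 0.80 SD, a baseline correlation of 0.7 and a baseline-adjusted completers analysis.

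| Assumed dropout | Exercise arm | Control arm | Completers estimate |
|---|---|---|---|
| Completely random | 20% | 20% | 0.80 |
| Depends on baseline only | 21% | 17% | 0.80 |
| Higher in exercise-arm children doing badly | 21% | 10% | 0.90 |

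The bias is nil in the first two rows and about +0.10 SD in the third.

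**5. Dropout before follow-up that depends on the end-of-programme value.** Completers give 0.87 against a true 0.80. Keeping the lost children and imputing them from their end-of-programme value gives 0.80. If the end of the trial means the follow-up visit, the rule discards exactly these children.

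In none of these cases does the restriction remove bias.

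**The case against.** The strongest reply is that this is one sentence about a secondary analysis. The main analysis imputes every randomised child, so neither the 0.14 nor the 0.20 SD applies to it. That stands.

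Four stronger readings are tempting, and the article does not support them.

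- *Every dropout is excluded.* Not established. The end of the trial is undefined, and a child who stops the sessions but attends the assessments stays in.
- *The restriction is itself the source of bias.* Too strong. With adjustment for age and baseline, a completers analysis is unbiased when dropout is random or depends only on those covariates, as the simulation shows. The supportable statement is that the restriction does not prevent bias and can leave or add it.
- *The main and sensitivity analyses omit the same children.* They do not. They may agree for a different reason: both can rest on the same missing-at-random assumption.
- *The restriction governs the intention-to-treat imputation.* That would contradict the promise to analyse all randomised children, but the sentence names sensitivity analyses.

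It is also fair to say that the type and range of a sensitivity analysis are commonly left to a statistical analysis plan, which is not shown here. Their absence is not the point. The point is that the article does fix a rule, and the rule does not serve its stated purpose. The cited source is not among the documents and was not relied on either way.

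A related but separate conflict lies in Section 2.4: "The experimental group individuals should complete at least 80% of the sessions and all the evaluations to be considered in the analysis". This does not fit the intention-to-treat sentence, and the two sections need to be reconciled.

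**Conclusion.** The point holds in limited form. The sensitivity imputation omits at least all children lost during the programme without a final assessment. It also omits those lost before the one-month follow-up if that visit is the end of the trial. It is close to a completers analysis, and it cannot test what the main imputation assumes about those children. The stated reason for the restriction is not borne out.

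The possible bias in the completers estimate runs from none to about 0.14 SD (20% dropout) or 0.20 SD (30% dropout) in the one-arm case. The dropout rates, their confinement to the exercise arm, and the correlations of 0.5 and 0.6 are all assumptions. The sentence leaves the main intention-to-treat estimate unchanged; what is lost is a meaningful test of it. The sentence should be changed, but it does not undermine the primary analysis.

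**What to change.** Replace the sentence in Section 2.8 so that:

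- the sensitivity analysis keeps all randomised children and varies the assumption about their missing outcomes, for example by delta-adjusted multiple imputation;
- the shift is made in the unfavourable direction for each outcome. On sections A and B of the behavioural checklist (Section 2.6) a higher score is worse, so the shift there is upward;
- the range of shifts is stated in advance and marked as an assumption. Section 2.3 does not name the metric of its 0.40, so a range tied to that figure must say how it is read;
- any analysis of children with both baseline and end data is labelled a supplementary completers analysis;
- the clause about preventing estimation bias is deleted;
- the end of the trial is defined as either the end-of-programme or the one-month assessment.

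The cost is a few lines of wording and a few extra runs on the imputed data sets. No additional data are needed.

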### 2.5. Randomisation and Blinding

Participants will be randomly assigned to the experimental (SSE) or control (usual care) group using The Research Randomizer (http://www.randomizer.org) (accessed on 8 July 2021) [58], with a computer-generated randomisation sequence (1:1). A member of the team not involved in this trial will handle this task, protecting the assignment in a password-protected computer file. Participants will be aware of which group they have been assigned to, but the researchers who will carry out the measurements and analyses will not.

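### The by-protocol analysis filters attendance in the experimental arm only, and the eligibility section extends that filter to the analysis in general, against the intention-to-treat statement; neither analysis is named primary

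*Protocol article*

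**What the plan says.** Four statements in the Protocol article bear on who is analysed.

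- **Section 2.8, intention-to-treat:** "All randomised participants will be considered for the analysis in its group", with multiple imputation for missing data and a repeated-measures analysis of covariance adjusted for age and baseline.
- **Section 2.8, by protocol:** the same analyses, but "only for participants who attend at least 80% of the program sessions". No arm is named.
- **Section 2.4, at the end of the eligibility criteria:** "The experimental group individuals should complete at least 80% of the sessions and all the evaluations to be considered in the analysis". An arm is named here, completion of all evaluations is added, and the rule is not limited to the by-protocol analysis.
- **Section 2.7, controls:** they "will continue with their usual treatments and will only be present for the assessment sessions".

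The programme length comes from Section 2.7: "Participants will perform the SSE intervention program twice a week for 9 weeks". Section 2.8 introduces the intention-to-treat and by-protocol analyses together and does not say which gives the trial's main answer.

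**The concern.** There are two linked problems.

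First, the attendance filter can act on one arm only. Children in the experimental arm who come to few sessions are removed, while the controls who would have behaved in the same way stay in. The article itself suggests why attendance could track ability. Its Discussion relates motor performance to severity of the disorder, and says that low physical competence and movement difficulties can lead children to reject physical activity. If children with poorer balance attend less, the filtered comparison favours the programme even when the programme does nothing.

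Second, Section 2.4 as worded carries the same filter, plus a completeness rule, into the analysis generally. Someone following Section 2.4 would drop randomised children from the experimental arm whom Section 2.8 says must be kept. With no analysis named primary, the article does not settle which set of children yields the trial's result.

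**Working it through.** **1. The plan's own figure.** Section 2.3 gives 52 children (26 per arm) for two-sided alpha 0.05, 80% power and an effect size of 0.40 labelled large. Read as Cohen's f = 0.40, which for two equal groups is d = 2f = 0.80, a two-sample t-test with 26 per arm has power 80.7%. The figure reproduces and is not disputed. It gives a yardstick: the planned effect is 0.80 SD.

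**2. The cut-off.** 2 sessions × 9 weeks = 18. 0.80 × 18 = 14.4. 14/18 = 77.8% fails and 15/18 = 83.3% passes, so the rule means at least 15 sessions.

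**3. Who can meet it.** A control attends 0 of 18, so 0 of 26 controls can satisfy the Section 2.8 wording taken alone. The target includes the effect "concerning the time and group × time interaction", which needs both arms. Section 2.4 resolves this by tying the rule to the experimental group. The operative comparison is therefore experimental children with at least 15 sessions against all 26 controls.

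**4. The two sections side by side.**

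| | Section 2.4 | Section 2.8, intention-to-treat | Section 2.8, by protocol |
|---|---|---|---|
| Arm filtered | experimental | none | not named |
| Attendance | at least 80% | not required | at least 80% |
| All evaluations | required | not required (imputed) | not mentioned |
| Applies to | the analysis, unqualified | this analysis | this analysis |

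Section 2.4 conflicts with the intention-to-treat column. If Section 2.4 is taken to define only the by-protocol set, it still differs from Section 2.8, because only Section 2.4 demands all evaluations.

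**5. Size of the selection effect.** The article gives neither retention nor correlation, so both are assumed. Let k be the fraction of the experimental arm retained, ρ the correlation of attendance propensity with outcome, and z the (1 − k) normal quantile. With no treatment effect, the mean of the retained children exceeds that of the controls by

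bias = ρ × φ(z) / k (in SD).

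- k = 0.80: φ(z)/k = 0.280/0.80 = 0.350. For ρ = 0.3, 0.105; for ρ = 0.5, 0.175.
- k = 0.70: φ(z)/k = 0.348/0.70 = 0.497. For ρ = 0.3, 0.149; for ρ = 0.5, 0.248.
- ρ = 0: 0 at any k.

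The unadjusted range is thus about 0.11 to 0.25 SD. Against the planned 0.80 SD, that is 0.105/0.80 = 13% to 0.248/0.80 = 31%. Simulated two-sided type I error (10,000 runs, nominal 5%) was 6.2% and 8.5% at k = 0.80, and 7.6% and 12.9% at k = 0.70, for ρ = 0.3 and 0.5.

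**6. After baseline adjustment.** The planned model adjusts for baseline. With baseline–outcome correlation r and attendance–baseline correlation ρ_b, the bias becomes approximately φ(z)/k × (ρ − r × ρ_b).

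- If attendance relates equally to baseline and outcome (ρ_b = ρ) and r = 0.7 (both assumed), the step 5 values are multiplied by 1 − 0.7 = 0.3. This gives 0.03 and 0.05 SD at k = 0.80, and 0.04 and 0.07 SD at k = 0.70, with type I error about 5.6% to 6%.
- With r = 0.5 the factor is 0.5, and the largest value is 0.248 × 0.5 = 0.12 SD.
- If attendance relates to outcome but not to baseline (ρ_b = 0), adjustment removes none of the bias.

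**7. Loss of power.** At 90%, 80% or 70% retention (assumed) the set is 23, 21 or 18 against 26, and power at d = 0.80 falls from 80.7% to 78.2%, 76.1% or 72.2%.

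**The case against.** The strongest reply is that this is an ordinary secondary analysis. With a usual-care control, adherence can only be filtered in the active arm. Intention-to-treat is planned, comes first and uses all randomised children. The by-protocol paragraph reads as a restriction of it, and details of analysis sets are commonly left to a statistical analysis plan. Baseline adjustment may also leave little bias. Much of this stands: the trial is not invalidated, and the bias may be negligible. It does not answer the conflict between Sections 2.4 and 2.8, which are both stated rules and cannot both be followed. Nor does it make the filtered comparison a randomised one.

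Three stronger readings are tempting, and the article does not support them.

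- *The by-protocol set contains no controls, so the comparison cannot be run.* That follows only from Section 2.8 read alone. Section 2.4 names the experimental group, so the missing arm in Section 2.8 is a fault of wording.
- *Forming the set unblinds the analyst.* Section 2.5 says that of group assignment "the researchers who will carry out the measurements and analyses will not" be aware. Nothing says the blinded analyst handles attendance records. Someone else could supply a membership flag that counts every control as included.
- *The by-protocol result will look better, and the better result will be reported.* The direction depends on the unknown sign of the attendance–outcome relation, and nothing in the article indicates selective reporting.

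**Conclusion.** The point holds as a fault in what the article fixes. The by-protocol comparison, on its operative reading, sets selected attenders (15 or more of 18 sessions) against unselected controls, so randomisation no longer protects it. Section 2.4, as worded, contradicts the intention-to-treat statement in Section 2.8, and no analysis is named primary. The contradiction rests on the text alone and needs no assumption.

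The size of the bias does rest on assumptions. At 70–80% retention and an attendance–outcome correlation of 0.3–0.5 it is about 0.11–0.25 SD unadjusted. It is about 0.03–0.07 SD after baseline adjustment if attendance relates equally to baseline and outcome and these two correlate at 0.7. It is zero if attendance is unrelated to outcome. These figures are illustrative and not a prediction for this trial. The change should be made, but the planned intention-to-treat analysis keeps the matter from being critical.

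**What to change.** 1. State in Section 2.8 that intention-to-treat on all 52 randomised children is the primary analysis.
2. Reconcile Sections 2.4 and 2.8 so that the 80% attendance and all-evaluations rule excludes nobody from that analysis.
3. State that the attendance filter applies to the experimental arm only, give it as at least 15 of 18 sessions, and say whether complete evaluations are also required and of whom. Label this comparison supportive and non-randomised.
4. For the effect of attending, use an instrumental-variable (two-stage least squares) estimate on all 52 children. Allocation is the instrument, the proportion of the 18 sessions attended is the exposure, and baseline and age are covariates.

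Items 1 to 3 cost only wording. Item 4 costs one extra model. Because controls attend no sessions, the estimate is roughly the intention-to-treat difference divided by the mean proportion attended in the experimental arm. If that mean were 0.80, for example, both the estimate and its interval would be about 1/0.80 = 1.25 times as large. It therefore adds interpretation and not power. It assumes that allocation affects outcome only through attendance and that the effect is linear in sessions attended. Both assumptions should be stated with the result.

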## 3. Discussion

This study will be the first to use an SSE program to improve sensory, motor, and cognitive skills in children and adolescents with ASD diagnoses. To the best of our knowledge, it will be the second in the world carried out in children [55]. We hypothesise that the SSE programme will lead to sensorimotor improvements in children with ASD because of an improvement in sensory integration and balance and postural control. Moreover, because of the high component of planning, sequencing, change of criteria, and monitoring, we also expect positive results in the enhancement of attention and executive functions.

Children and adolescents with ASD present cognitive-behavioural, socio-communicative issues and sensorimotor challenges that cause issues in both fine and motor skills and coordination. The relationship between motor performance and movement quality is closely related to the severity level of the disorder [67,68]. Moreover, motor [35,37,43], sensory [69], cognitive [46], and socio-communicative skills impairments [45,70,71,72] impact the development of their occupations, including activities of daily living, learning, leisure, and social participation in their communities [73,74]. If this program is effective, it should be implemented in schools, clinics, and associations specialising in the education and treatment of ASD individuals because it is an innovative and easy-to-apply program, resulting in a tool for the improvement of the aforementioned skills and the inclusion of these children and adolescents.

In the long term, we also hope to increase the time spent performing physical exercise as a protective factor for their health and quality of life, adapting the activity to their characteristics and considering the barriers. In 2008, Spain ratified the Convention on the Rights of Persons with Disabilities [75], committing itself to carry out policies to improve the social participation of all people in the spheres of daily life, including school and leisure. The right of people with ASD to participate in activities is also included in the Sustainable Development Goals, being directly related to goals (3) Health and well-being, (4) Quality education, and (10) Reduction of inequalities [76]. Therefore, we hope that this project will be a small contribution to fulfilling the rights of people with ASD. One of the most important manifestations of motor skills is the practice of physical activity and sports. Several barriers to physical activity practice in children and adolescents with ASD are reported. Families consider it important for their children with ASD to exercise, but they demand support so that they can participate in these activities, as they are socially highly demanding, occur in changing contexts, and may have rules that are difficult to interpret. All the previous factors, together with their low physical competence and movement difficulties, can cause rejection [77]. Additionally, adults with ASD indicate a lack of motivation, interpersonal difficulties, and problems with sportive activities, including the type of activity, transportation or cost [78]. This limited participation in physical activities causes both preadolescents and adolescents with ASD to have a worse fitness level [79] and a higher body mass index compared with typically developed children and adolescents [80], which causes them to be at risk of suffering from pathologies related to physical inactivity, such as diabetes, hypertension, coronary and cerebrovascular diseases, and overweight/obesity, among others, which increase mortality [81,82].

